#### 12.2.1 Include

- Failure to tolerate oxygen therapy e.g. failing to tolerate face mask, heated humidity/facial sore
- Nose bleeds
- Incorrect set-up of equipment/equipment failure.

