**Figure 2:** Williams et al proposed a model of the relationship between inspired gas humidity and temperature, exposure time and mucosal function based on the data in **Figure 1**. This figure shows how the mucociliary transport system can be affected by altering the humidity levels and how that effect is increased during poor health or respiratory illness.

It is for these reasons that heated, humidified oxygen is routinely given on intensive care. Studies in intubated adults and children have shown that maintaining airway temperature close to body temperature beneficially affects lung function, mucus clearance and in NIV, patient compliance.

With portable humidification devices becoming more widely available, it is now possible to give heated humidified oxygen in acute emergency situations and on inpatient medical wards. To date only one study has examined its effect in acute asthma. This was a study in children (6-17yrs) whose initial nebulised bronchodilator therapy only was driven by humidified oxygen, either at room temperature or at 40°C. This short intervention was well tolerated and peak flows increased more following nebulisation with heated humidified oxygen than with humidified oxygen at room temperature. Overall however, there is a dearth of evidence to support its use in either children or adults, a situation recognised by both the *British Thoracic Society (BTS) Guidelines for Emergency Oxygen Use* (2008) and the 2012 update of the *BTS Guideline on the Management of Asthma*.

Currently in the UK, children (and adults) with acute severe asthma, receive cold (15°C), dry (un-humidified) oxygen in the A&E department for between one and four hours prior to transfer to the ward. If admitted, they may or may not receive humidified oxygen depending on their local hospital asthma guidelines. Through the National Paediatric Respiratory Nurses Group, we surveyed the use of humidified oxygen nationwide, obtaining responses from 17 paediatric departments from Exeter to Melrose. No hospital gave humidified oxygen in A&E and over half didn't give humidified oxygen following admission to medical wards. Of those that gave humidified oxygen, approximately a quarter could also give warmed humidified oxygen. All

surveyed felt that any study on the use of humidified oxygen in children with acute severe asthma would be worthwhile.

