## 10.3 Procedures for Assessing Safety

Adverse events (AEs) (see section 12.1-2) will only be reported for participants where consent has been obtained and the causal relationship to the trial treatment (oxygen or delivery equipment) has been assessed and judged by the investigator to be related to the trial treatment, which occurs from the start of randomised treatment until final study assessment. The events should be recorded on a Related Adverse Event Form, which should be transmitted to the CTU within seven days of the clinical research team becoming aware of the event.

All related AEs should be followed until satisfactory resolution or until the investigator responsible for the care of the participant deems the patient to be stable.

Follow-up information for an AE should be noted on the related AE form under the heading marked 'outcome'.

When reporting AEs the investigator responsible for the care of the participant should apply the following criteria to provide information relating to event outcomes: resolved; resolved with sequelae (specifying with additional narrative); not resolved/ongoing; ongoing at final follow-up; unknown.

There are no serious adverse events anticipated which are related to the study interventions.

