### 11.2 Outcome Measures Prioritisation and Consensus

The following outcome measures will be examined in this study:

- Length of time in oxygen
- Time until treatment 'stepped down' to hourly, two-hourly and four-hourly nebulised therapy
- Yung's asthma severity score
- Number of Salbutamol and Ipratropium Bromide nebulas required by each patient
- Requirement for escalation of treatment (i.e intravenous Salbutamol/Aminophylline or HDU/PICU)
- Adverse events/tolerability
- Length of stay in hospital

These outcomes have been identified as relevant and important in a previous exercise involving consumers and paediatricians (MCRN Respiratory and General Paediatrics Clinical Studies Groups), however their relative importance has not been assessed. A consensus exercise will be undertaken to establish which outcome(s) will be taken forward to the definitive randomised controlled trial. This will involve: (1) trial participants/families (research nurses will give a one-page questionnaire to parents/guardian once the patient has become stable and has come out of oxygen), (2) lay members of the study Steering Group, (3) the MC Young Person's Advisory Group, (4) Asthma UK, (5) MC Respiratory and General Paediatric Clinical Studies Groups.

In addition, outcome measure stability, feasibility of data collection and missing data events from the pilot study will contribute to selection of the most appropriate outcome(s) based on both consensus and feasibility.

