## 12 Safety

### 12.1 Terms and Conditions

#### **Adverse Event (AE)**

Any untoward medical occurrence in a subject to whom a medicinal product has been administered, including occurrences which are not necessarily caused by or related to that product.

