### 12.2 Notes on Adverse Event Inclusions and Exclusions

Only related and unexpected adverse events/ severe adverse events will be reported. For the purposes of this study, a related event is one related to the intervention/therapy, not the underlying condition itself. For related and unexpected events:

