#### 12.2.2 Do not include

- Medical or surgical procedures
- Pre-existing disease or conditions present before treatment that do not worsen
- Situations where an untoward medical occurrence has occurred
- The disease being treated or associated symptoms/signs unless more severe than that expected for the patient's condition
- Changes in the amount of oxygen administered immediately following change in route of oxygen administration

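### Section 12.2.1 makes set-up errors and equipment failures reportable as adverse events with no consequence for the child required, which does not fit the definition in 12.1 and is not resolved by 12.2.2

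*Protocol*

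**What the plan says.** Section 12.1 opens its definition of an adverse event with "Any untoward medical occurrence in a subject to whom a medicinal product has been administered". Section 12.2 then narrows what is sent in: "Only related and unexpected adverse events/ severe adverse events will be reported". Two lists follow.

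- The list to include (12.2.1) has three items: failure to tolerate the oxygen therapy, nose bleeds, and "Incorrect set-up of equipment/equipment failure". The third has no condition about an effect on the child.
- The list not to include (12.2.2) contains, as printed, "Situations where an untoward medical occurrence has occurred".

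Section 10.3 sets the route. An event is reported where "the causal relationship to the trial treatment (oxygen or delivery equipment) has been assessed" and the investigator has judged it related. The event must be one "which occurs from the start of randomised treatment until final study assessment". It goes on a Related Adverse Event Form, due at the trials unit within seven days.

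Section 11.2 lists "Adverse events/tolerability" as an outcome, as do section 1 and section 2.2, and it is among the outcomes from which those for the definitive trial will be chosen. Section 11.4 plans summary statistics for the main outcomes, without formal tests.

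**The concern.** A device or set-up fault that is noticed and corrected before it affects the child is not a medical occurrence. Under 12.2.1 it is nevertheless sent in as an adverse event. Sites that apply 12.1 will leave it out and sites that apply 12.2.1 will put it in, so the same fault can be classified differently from site to site.

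The arms also differ in how much there is to set up. Under 9.3 the heated arm needs a humidifier with a temperature setting, an oxygen therapy system and water kept topped up. The cold humidified arm needs a nebuliser unit, a water bottle and wide-bore tubing. The standard arm uses wall oxygen through a mask and later, where appropriate, nasal cannulae. The survey in 2.1 found that "No hospital gave humidified oxygen in A&E", so emergency staff may be less used to the humidifying equipment.

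At stake is how a listed outcome is read. If harmless faults enter the adverse event figures, a humidified arm may look less safe or less well tolerated when what it shows is a practical problem with equipment. That practical problem is worth knowing in a pilot, but under feasibility and adherence, where it can be acted on.

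**Working it through.** The check is mainly a comparison of text. Three kinds of event are set against each provision:

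| Event | 12.1 definition | 12.2.1 list | 12.2.2 as printed | 12.2.2 if a 'not' was dropped |
|---|---|---|---|---|
| Nose bleed related to the treatment | adverse event | include | exclude | not excluded |
| Equipment fault followed by a medical occurrence | adverse event | include | exclude | not excluded |
| Equipment fault, child unaffected | not an adverse event | include | not excluded | exclude |

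1. As printed, 12.2.2 removes the first two rows, which 12.1 and 12.2.1 both want reported, and leaves only the harmless fault. This cannot be what was meant.
2. With 'not' restored, 12.2.2 agrees with 12.1 in every row, but it contradicts 12.2.1 in the third.
3. On neither reading can all three provisions be followed together. The harmless fault is in dispute on both: 12.2.1 includes it and 12.1 does not recognise it.

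**The reporting window.** Section 10.3 starts reporting when randomised treatment starts. A set-up fault that prevents or delays that start comes before the window opens. Section 13.2 asks for a reason when a clinician gives alternative treatment after trial entry, so some of these faults will be recorded there. The protocol describes no dedicated record for the rest.

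**Size.** The protocol states no figure to reproduce here. The only usable input is 30 children per arm (section 11.3). If k children in an arm are recorded with an adverse event solely because of a harmless fault, that arm's proportion with an adverse event rises by k/30:

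- k = 1: 1/30 = 3.3 percentage points
- k = 2: 2/30 = 6.7 percentage points
- k = 3: 3/30 = 10.0 percentage points

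The values of k are assumptions chosen to show scale. The protocol gives no fault rate for any arm.

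**The case against.** The strongest reply is that reporting equipment problems is deliberate. Section 9.1 describes a comparison of three methods of giving oxygen, and 10.3 places the delivery equipment within the trial treatment. A fault in that equipment is then a property of the intervention, and a higher count in one arm would be a true finding. This stands, and it is the reason to keep the reports. It does not show that a fault without medical consequence belongs in the same category as a nose bleed.

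A second reply is that 12.2.1 can be read as a list drawn from adverse events already meeting 12.1, so that only faults with a medical consequence count. That reading is possible, but the item does not say so, and 12.2.2 as printed points the other way.

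A third is that the analysis is descriptive, no test or sample size depends on this, and a statistical analysis plan may tabulate event types separately. This limits the weight of the point. A later plan could separate the types, but it could not restore faults that were never reported or undo differing classification at sites.

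A reader might also infer more than the text supports:

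- **That faults are counted as patient harm.** The protocol does not say this. The outcome covers tolerability as well as adverse events, and no section pools the three listed items into one figure.
- **That faults will arise mainly in the humidified arms.** This is an inference from the equipment described. Masks and cannulae in the standard arm can also be set up wrongly, and 3.1 says that all three treatments are in routine ward use.
- **That adverse event rates would nearly double.** Assuming 10% true events in every arm, independent faults in 10% of a humidified arm and none in the standard arm, the figures are 1 − 0.90 × 0.90 = 19% against 10%. Every input is assumed, and zero faults in the standard arm is the extreme case.
- **That faults before treatment starts are all lost.** Section 13.2 captures those that lead a clinician to give something else.

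**Conclusion.** The definitional conflict holds on the text alone: 12.1, 12.2.1 and 12.2.2 cannot be applied together to a fault that leaves the child unaffected. The effect on the results is a possibility. If sites follow 12.2.1, and if harmless faults are commoner where there is more equipment, the descriptive adverse event figures in the humidified arms may be higher without any difference in clinical events. Each such child moves an arm of 30 by 3.3 percentage points. The direction rests on the equipment described in 9.3, and the number of such children is unknown. No hypothesis test, sample size or stopping rule is affected. The point is worth correcting because adverse events/tolerability is a candidate outcome for the definitive trial and the change is small.

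**What to change.** Reconcile sections 10.3, 12.1, 12.2.1 and 12.2.2 in one edit:

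- Keep set-up and equipment faults reportable to the trials unit, under their own device/procedure fault category. Deleting the item from 12.2.1 outright would lose the only explicit instruction to send them in.
- Record these faults from randomisation onwards, including failure to start the allocated treatment, and tabulate them by arm under feasibility and adherence.
- Count a fault as an adverse event only if an untoward medical occurrence resulted.
- Correct the item in 12.2.2 so that it no longer excludes events meeting the definition in 12.1.

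The cost is the rewording, one extra CRF line and one extra table. Reported adverse event counts may be lower, with the harmless faults shown separately.

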#### 12.2.2 Do not include

- Medical or surgical procedures
- Pre-existing disease or conditions present before treatment that do not worsen
- Situations where an untoward medical occurrence has occurred
- The disease being treated or associated symptoms/signs unless more severe than that expected for the patient's condition
- Changes in the amount of oxygen administered immediately following change in route of oxygen administration

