#### **Serious Adverse Event (SAE)**

Any adverse event, that:

- results in death
- is life-threatening\* (subject at immediate risk of death)
- requires in-patient hospitalisation or prolongation of existing hospitalisation\*\*
- results in persistent or significant disability or incapacity, or
- consists of a congenital anomaly or birth defect
- is an other important medical event that may jeopardise the subject\*\*\*

\*‘life-threatening’ in the definition of ‘serious’ refers to an event in which the patient was at risk of death at the time of the event; it does not refer to an event which hypothetically might have caused death if it were more severe.

\*\*Hospitalisation is defined as an inpatient admission, regardless of length of stay, even if the hospitalisation is a precautionary measure for continued observation. Hospitalisations for a pre-existing condition, including elective procedures that have not worsened, do not constitute an SAE.

\*\*\*Other important medical events that may not result in death, be life-threatening, or require hospitalisation may be considered a serious adverse event/experience when, based upon appropriate medical judgment, they may jeopardise the subject and may require medical or surgical intervention to prevent one of the outcomes listed in this definition.

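### Section 12.2.2 tells sites not to report situations that match the protocol's own definition of an adverse event, contradicting the include list and the reporting rules

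*Protocol*

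**What the plan says.** Section 12.1 defines an adverse event as "Any untoward medical occurrence in a subject to whom a medicinal product has been administered", whether or not the product caused it. It builds the serious adverse event on that definition: "Any adverse event, that" meets one of the listed seriousness criteria.

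Section 12.2 sets the reporting rule: "Only related and unexpected adverse events/ severe adverse events will be reported". Two lists follow under one lead-in.

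- Section 12.2.1 (to be included) names "Failure to tolerate oxygen therapy e.g. failing to tolerate face mask, heated humidity/facial sore", nose bleeds, and "Incorrect set-up of equipment/equipment failure".
- Section 12.2.2 (not to be included) has five bullets. The third is "Situations where an untoward medical occurrence has occurred".

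Section 10.3 separately requires events that the investigator judges related to the oxygen or its delivery equipment to be reported: "The events should be recorded on a Related Adverse Event Form", which goes to the trials unit within seven days. It refers to Sections 12.1 and 12.2 for what an adverse event is.

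"Adverse events/tolerability" is a listed outcome in Sections 1, 2.2 and 11.2. Under Section 14.5 the Trial Management Group reviews serious adverse events across sites.

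**The concern.** A list of what not to report should carve out limited categories. The other four bullets of 12.2.2 do so: procedures, unchanged pre-existing disease, expected signs of the asthma itself, and changes in oxygen amount just after a change of route. The third bullet instead restates the definition of what is to be collected, with no qualifier. The polarity appears to be reversed.

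This is an operational instruction to sites, so it can affect the data. Collection is already narrow: Section 10.3 takes only events judged related, and Section 12.2 adds that they be unexpected. A further exclusion that some staff apply and others ignore would make counts depend on how each hospital reads the list. The analysis would not reveal this. Section 11.4 assesses the proportion of missing values for each outcome, but an event that was never reported looks like no event, not like a missing value. Section 11.2 will use feasibility of collection and missing data to choose outcomes for the definitive trial, so a misleadingly clean record for this outcome could carry forward.

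**Working it through.** The plan gives no figure on this point, so the check is textual.

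**Step 1: definition against exclusion.** By Section 12.1 every adverse event is an untoward medical occurrence, and every serious adverse event is an adverse event. The third bullet of 12.2.2 excludes situations in which such an occurrence has taken place. Taken literally, the excluded set therefore contains every adverse event and every serious adverse event so defined.

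**Step 2: the two lists against each other.** The last column shows the effect of inserting 'not' into the bullet.

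| Event | Meets the 12.1 definition? | 12.2.1 | 12.2.2 bullet as written | Bullet with 'not' inserted |
|---|---|---|---|---|
| Nose bleed | Yes | Include | Excluded | Not reached |
| Facial sore | Yes | Include | Excluded | Not reached |
| Mask not tolerated, no injury | Arguable | Include | Excluded if counted as a medical occurrence | Excluded if not so counted |
| Equipment fault with a medical consequence | Yes | Include | Excluded | Not reached |
| Equipment fault with no medical occurrence | No | Include | Not reached | Excluded |
| Other related, unexpected serious event | Yes | Not named; reportable under 10.3 and 12.2 | Excluded | Not reached |

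As written, the bullet conflicts with the include list for nose bleeds, facial sores and equipment faults with a medical consequence. It conflicts with Sections 10.3 and 12.2 for any other related, unexpected event. It does not reach an equipment fault that harmed nobody. With 'not' inserted, that fault becomes the conflict, so the one-word correction is not enough alone.

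**Step 3: is the conflict resolved elsewhere?** Both lists stand under the same lead-in on related and unexpected events, so they govern the same events. No section says which list prevails.

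**Step 4: is it an artefact of the text?** The bullet is a complete, grammatical sentence fragment with no gap or redaction mark. Nothing suggests lost text.

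Two readings are assumed. The definition speaks of a medicinal product; I take oxygen as covered, because Section 10.3 applies the adverse event rules to the oxygen and its delivery equipment. The word 'severe' in the Section 12.2 rule is read as the serious events of Section 12.1.

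**The case against.** The strongest answer is that the bullet is recognisably a slip and that staff have better instructions to follow. Section 10.3 has its own reporting duty, form, deadline and follow-up. Section 12.2 repeats the duty, and 12.2.1 names the events most likely with masks and humidifiers. A nurse who sees a nose bleed has a specific instruction to report it, against one generic bullet. The rest of 12.2.2 also presupposes reporting: the bullet on the disease under treatment keeps signs reportable when they are worse than expected for the patient, which makes sense only if untoward occurrences are reportable.

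Much of this stands, and it limits the consequence. A reader might infer that the rule removes every event, or that sites would report nothing. The documents do not support that: three other sections direct sites to report related events, and a harmless equipment fault lies outside the bullet even on its literal wording. A reader might also infer that a count of zero would be turned into an upper confidence limit on the event rate and presented as evidence of tolerability. Section 11.4 plans summary statistics for the main outcomes without formal hypothesis tests, and no section plans such a limit.

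What does not stand is that the error can be left because sensible staff would guess the intent. Section 10.3 points to Section 12.2, which is where the reporting rule is spelled out, and the protocol offers nothing to settle the conflict. Nor does it answer the point that Section 3.1 describes all three treatments as routine on wards: in the survey in Section 2.1, none of 17 departments gave humidified oxygen in A&E, so tolerability there is something the pilot should observe reliably.

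**Conclusion.** The contradiction is real and plain on the face of the protocol. One bullet of 12.2.2 excludes what 12.1 defines as an adverse event and conflicts with 12.2.1, 12.2 and 10.3. Because it is an operational reporting rule for a listed outcome and for oversight of serious events, it is an error to correct and more than a clerical blemish.

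The expected effect is contradictory instructions, with inconsistent or under-reported events across the four hospitals named in Section 4. How many events would be lost among the planned 90 children (30 per arm) cannot be derived: the protocol gives no expected event rate, and the loss depends on which instruction each site follows.

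That a 'not' was dropped is the most natural explanation, but it is inferred from the sense of the list; the protocol does not say so.

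**What to change.** 1. Correct the third bullet of 12.2.2, most likely so that it refers to situations where an untoward medical occurrence has not occurred. The sponsor should confirm that this was the intent. Deleting the bullet would also remove the contradiction.
2. State that 12.2.1 takes precedence over 12.2.2 where they appear to conflict. This clause is needed if the bullet is kept with 'not': otherwise equipment set-up errors or failures without a medical occurrence, and perhaps simple mask intolerance, would be excluded although 12.2.1 asks for them.
3. Read the corrected list against Sections 10.3, 12.1 and 12.2 and reconcile them, so that sites have one consistent reporting rule.

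The cost is a correction of one word or one bullet, one added sentence, and a note to the four sites. No change to design, sample size or analysis is involved.
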